**Figure 3 figure3:**
[figure not shown]
Communities Organizing for Power through Empathy (COPE) conceptual model. S2: COPE session 2; S3: COPE session 3.

**Figure 4 figure4:**

Communities Organizing for Power through Empathy (COPE) session topics.

### Attention Control Arm: House Meetings

Parallel to the intervention arm, participants in clusters randomized to the control arm will complete assessments before content delivery at the first 3 time points. After the first 2 assessments, they will participate in house meetings—group deliberative conversations, sometimes referred to as listening sessions—following a model regularly practiced by TBR [84,85] before participating in the COPE intervention at their third meeting and just after completing their third assessment. The house meeting is a group session that lasts approximately 1.5 hours and engages participants in a discussion about a specific question posed by the facilitators. At the first house meeting, and after administering the first assessment, participants are prompted to discuss “How are you a caregiver in your everyday life? What does it mean to you to be a caregiver?” or a similar question. Each participant is encouraged to share at least once. The facilitator is not necessarily a mental health professional, and no therapy is provided. At the end of the house meeting, participants are reminded of the date for the next meeting. The second house meeting follows the same protocol with a modified prompt question. After completing the third assessment, participants engage in the COPE intervention.

### Study Outcome Measures

We will examine measures of implementation to respond to aim 1 and respond to aim 2 by assessing 3 levels of outcomes (primary, secondary, and tertiary) from the SW-CRT (see Table 1 for a detailed list of outcomes and measures). To address aim 1, we will use the Consolidated Framework of Implementation Research [76] to examine factors that affect intervention implementation and program effectiveness, as well as perceptions of feasibility, acceptability, and cultural appropriateness. We will use standardized measures of acceptability (Acceptability of Intervention Measure [AIM]), appropriateness (Intervention Appropriateness Measure [IAM]), and feasibility (Feasibility of Intervention Measure [FIM]), as well as items related to facilitator preparation and logistics and intervention acceptability developed by the research team. The AIM measures degree of satisfaction with intervention, the IAM its relevance and fit, and the FIM perception of potential for success within an organization. Each construct consists of 5 items rated on a 5-point Likert scale ranging from 1 (completely disagree) to 5 (completely agree). The measures have demonstrated acceptable fit and structural validity and reliability (Cronbach α=0.73-0.88) [86]. We are collecting these data via a survey, interviews, and focus groups conducted with CFs. In addition, we will analyze data from field notes, fidelity observations, interviews, and focus groups with institutional leaders and participants.

**Table 1 table1:** Study outcomes and measures

Measure		Time frame	Type	Source
**Psychological well-being**				
	Depression Anxiety Stress Scale Short Form	In the past week	Primary outcome	Lovibond and Lovibond [87], 1995
	Perceived Stress Scale	In the last month	Primary outcome	Cohen et al [88], 1983
**Social support**				
	Coping Self-Efficacy Scale	—^a^	Secondary outcome	Chesney et al [89], 2006
	Multidimensional Scale of Perceived Social Support	—	Secondary outcome	Zimet, et. al.[90], 1988
**Community connectedness**				
	Communities Advancing Resilience Toolkit	—	Tertiary outcome	Pfefferbaum et al [68], 2020
**Process evaluation**				
	Acceptability of Intervention	—	Acceptability	Weiner et al [86], 2017
	Intervention Appropriateness	—	Appropriateness	Weiner et al [86], 2017
	Feasibility of Intervention	—	Feasibility	Weiner et al [86], 2017

^a^Not applicable.

To address aim 2, we will collect cohort data on the outcome measures at the 5 assessment time points of the SW-CRT: baseline (T1), before session 2 (T2; 1 m after baseline), before session 3 (T3; 2 m after baseline), after the series (T4; 1 month after session 3), and 6 months after the series (T5). Figure 1 provides a visual of the design and timeline of survey measures. As the control arm switches to the COPE intervention after the T3 assessment, assessments pause until 1 month after session 3 so that T4 assessments align (Figure 1). Both arms complete the T5 assessment 6 months after session 3. As part of the CBPR process, the CBPR strategy team deliberated on the outcomes and measurements, coming to consensus on the final survey.

The primary outcomes and their measures assess individual mental health. Perceived stress is assessed with the Perceived Stress Scale (PSS), a 10-item scale that measures the degree to which a person rates situations as stressful [88], for example, how often respondents find their lives “unpredictable,” “uncontrollable,” or feel “overloaded.” Responses are scored on a 5-point Likert scale ranging from 0 (never) to 4 (very often). Total PSS scores range from 0 to 40, with higher scores reflecting higher perceived stress [91]. The 10-item Perceived Stress Scale has high internal reliability (Cronbach α=0.78-0.90) and has been translated and tested in >25 languages [88,91]. Depression, anxiety, and stress are measured with the Depression, Anxiety, and Stress Scale (DASS-21), a set of 3 self-report scales [87]. The 21 DASS-21 items ask about the presence of symptoms over the past week on a scale from 0 (did not apply to me at all) to 3 (applied to me very much or most of the time) [92,93]. Depression scores range from 0 to 4 (normal), 5 to 6 (mild), 7 to 10 (moderate), 11 to 13 (severe), and >14 (extremely severe). Anxiety scores range from 0 to 3 (normal), 4 to 5 (mild), 6 to 7 (moderate), 8 to 9 (severe), and >10 (extremely severe). Stress scores range from 0 to 14 (normal), 15 to 18 (mild), 19 to 25 (moderate), 26 to 33 (severe) and >34 (extremely severe). The DASS-21 has shown high internal reliability (Cronbach α=0.72-0.91) [92-94].

Secondary outcomes and their measures assess coping and social support. Coping self-efficacy is assessed with the Coping Self-Efficacy Scale (CSES), a 12-item measure of confidence in managing stress [89]. The CSES combines 3 subscales measuring distinct dimensions: problem solving, thought stopping, and obtaining social support. Each item is scored on an 11-point scale ranging from 0 (cannot do at all) to 10 (certainly can do). The CSES has high reliability and validity across diverse contexts (Cronbach α=0.76-0.93) [89]. Social support is measured with the Multidimensional Scale of Perceived Social Support (MSPSS), a 12-item measure combining 3 subscales examining perceived support from family, friends, and significant others [90,95]. Each MSPSS item asks at to what degree the respondent agrees that they felt supported by each group and is scored on a 7-point scale ranging from 1 (very strongly disagree) to 7 (very strongly agree). The MSPSS consistently demonstrates internal consistency across diverse populations in the United States and internationally (Cronbach α typically >0.90) [96-98].

The tertiary outcomes measure community resilience and use the Communities Advancing Resilience Toolkit (CART), a 21-item tool that assesses four domains, including (1) connection and caring, (2) community resources, (3) transformative potential, and (4) disaster management [68,99,100]. Each item asks participants to rate their agreement on a 5-point Likert scale from 0 (strongly disagree) to 4 (strongly agree). The 5 domains of the CART have demonstrated validity (connection and caring: Cronbach α=0.83; resources: Cronbach α=0.75; transformative potential: Cronbach α=0.90; and disaster management: Cronbach α=0.91) [101]. Data on relevant covariates, including demographic information (age, race, ethnicity, sex, household income, education, etc), will also be collected at baseline and, in cases where the item may vary over time (eg, self-rated health), repeated at each time point.

### Planned Analyses

#### Aim 1: Evaluate Factors That Affect Intervention Implementation, Efficacy, and Adoption

A mixed methods approach will be used to assess acceptability and feasibility of the COPE intervention. We will survey CFs, using the AIM, IAM, and FIM, to assess acceptability, appropriateness, and feasibility, along with items to assess preparation and satisfaction with the COPE intervention. In addition, intervention fidelity will be monitored in person by research team staff using a standard tool developed for the COPE intervention series. Qualitative assessments will also be conducted throughout the study, especially during the implementation and after the conclusion of every COPE series, and field notes will be taken at workshops. CFs, key leaders, and participants will be interviewed or participate in focus groups using semistructured interview guides.

We will conduct reflexive thematic analysis using the steps outlined and refined by Braun and Clarke [102,103] as a guide to analyze verbatim transcripts or field notes using the MAXQDA qualitative data analysis software. Each of the 6 steps of thematic analysis involves an iterative examination and reexamination of the data to ensure thematic coherence, generating themes from codes and refining the purpose and meaning of themes to clarify their interpretive story [102-104]. This approach permits reflexive discernment of differences across clusters and steps, accounting for nuance given variations in procedures, adjustment to delivery, and development of interpretative stories that convey deeper meaning around collective coping and community resilience [103].

#### Aim 2: Testing of Intervention Effects

Aim 2 will test the effectiveness of the COPE intervention on improvements in mental health symptoms (perceived stress, depression, anxiety, and stress), coping self-efficacy, perceived social support, and community resilience (see Table 1 for measures). The SW-CRT design involves clusters sequentially transitioning from control to intervention, allowing for within-cluster comparisons and accounting for time-dependent effects. The primary analysis for aim 2 will follow an intent-to-treat approach using a linear mixed model to examine within- and between-group differences across time. Missing data will be handled under the assumption that they are missing at random, using restricted maximum likelihood estimation, and we will assess the benefit of multiple imputation across missing values and conduct sensitivity analyses. The linear mixed model will account for the hierarchical structure of the data (eg, individuals, clusters, and time), and include fixed effects for the intervention arm, time, and covariates, such as age, ethnicity, and education. We will also include a random intercept for the clusters to assess between cluster variability and random slopes for time given the variability in time points between the clusters.

At time points 4 and 5, participants in the control arm will have transitioned to the intervention arm. To account for this transition, participants will be categorized based on their current condition (control or intervention) at each time point. This approach ensures that the analysis reflects the condition under which participants were exposed during each survey period. We will also conduct a sensitivity analysis to compare outcomes across time points 1 to 3 (before the switch) to time points 4 to 5 (after the switch). This will allow us to examine intervention effects during the period that the control group is unexposed to the COPE intervention. Results will be presented as regression coefficients with 95% CIs and *P* values, ICCs, and variance estimates for random effects.

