## Methods

### Overview and Study Design

This study uses a pragmatic mixed methods approach to examining the effectiveness and practical relevance of COPE in a real-world context [75]. We will collect and examine qualitative data to address aim 1, capturing contextual information about cluster-level and individual-level factors that influence the feasibility, implementation, and acceptability of COPE. We will approach aim 2, the test of intervention effectiveness, using a SW-CRT with a rolling enrollment design. As a pragmatic 2-arm SW-CRT, the study has two conditions or arms: (1) the intervention arm, in which clusters of participants begin by engaging in the COPE intervention, and (2) the attention control arm, in which clusters of participants begin by attending “house meetings” (listening sessions) before switching to the COPE intervention. A cluster is defined as a single CBO (or in a rare case, a pair of related CBOs). Clusters are eligible to participate if they are CBO members of TBR. Steps are clusters grouped by availability (ie, feasible start date as provided by CBO leadership). At the initiation of a step and before participant enrollment, clusters are randomized into study arms.

As a SW-CRT, every cluster will provide before and after observations, and will switch from control to intervention, but not at the same point in time (Figure 1) [74]. At study outset, clusters are assigned by the first author to 1 of 5 sequential steps: 2 in step 1, 4 in steps 2 and 3, and 6 in steps 4 and 5 (Figure 1). At the initiation of a step, clusters will be randomized by the first author into the intervention and control arms using a random number generator. Allocation into intervention or control arms will not be concealed at either the cluster or individual level, nor will clusters or participants be blinded, as doing so is not feasible given the group-based nature of the intervention and community-based nature of the study implementation. We will include controls to account for temporal and enrollment differences. Presurvey data collection will occur immediately before the start of the intervention within each cluster. After the third data collection time point, the clusters in the attention control arm will switch to receive the COPE intervention (see Figure 1 for the design timeline).

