To accomplish aim 1, we are using the Consolidated Framework for Implementation Research [76] to examine factors that affect intervention implementation and program efficacy, as well as standardized measures of perceptions of feasibility, acceptability, and cultural appropriateness. We will conduct quantitative assessments, interviews, and focus groups with community facilitators (CFs), institutional leaders, and participants (see Multimedia Appendix 1 for facilitator interview guide). In addition, to align with our CBPR approach, our research team includes a group of community members we refer to as the “CBPR strategy team” who guided the adaptation process that developed COPE and will guide the study design, implementation, and analysis of findings. For example, we presented them with options for measures of mental health and discussed the overall survey design. The team chose measures and approved the final survey instrument. We also worked with the team to discuss options for implementation of the COPE sessions and recruitment. As we analyze data, we will review findings and papers developed with the team, along with other community members. In our analyses for aim 1, we will integrate the methods by combining themes from interviews and focus groups with analyses of implementation measures.

To accomplish aim 2, we are collecting cohort data from participants in clusters in both arms assessed along measures of mental health, coping, social support, and community resilience at 5 time points (see Figure 1 for study design and data collection time points). Participants will complete assessments at each time point before content delivery using Qualtrics survey software loaded on a tablet. In cases where participants are unable to use a tablet (eg, discomfort with technology or visual impairment), they will complete the assessment on paper and research staff will enter the data into the software. Participants will be given a US $10 gift card at the completion of each questionnaire.

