### Potential Limitations

Although this study design presents a rigorous approach to evaluating the effectiveness and implementation of the COPE intervention, limitations should be considered. First, the SW-CRT design may introduce potential biases related to the sequential rollout of the intervention across clusters [74]. Clustering can occur because randomization happens on the group level, potentially generating high intracluster correlation, as participants within the same cluster may respond to COPE more similarly to each other than to those in other clusters. In addition, the clusters are grouped for randomization based on when they could reasonably begin the intervention, then randomized at different time points. This might impact the outcomes due to temporal context particularly as the intervention is introduced sequentially which requires a longer time to completion than would a parallel-group randomized controlled trial [117]. This prolonged duration can increase the risk of external factors, such as in environmental conditions (eg, hurricane season and winter), that may influence the implementation and effectiveness of the intervention [117,118]. We will implement several mechanisms for ensuring fidelity across clusters, including detailed fidelity checklists and monitoring of each facilitator’s initial delivery of the COPE intervention. In addition, to improve generalizability of our findings, we will control for cluster, as well as for step and important seasonal variations.

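### The primary model names a cluster intercept and time slopes but no cluster-by-time-point effect, so COPE intervals will be too narrow if clusters shift at single surveys

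*Protocol article*

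**What the plan says.** Under Planned Analyses, Aim 2, the primary analysis is a linear mixed model that will "include fixed effects for the intervention arm, time, and covariates, such as age, ethnicity, and education". For the random part: "We will also include a random intercept for the clusters to assess between cluster variability and random slopes for time". The reason given for the slopes is differing timing: "random slopes for time given the variability in time points between the clusters". The same paragraph says in general terms that the model respects individuals, clusters and time. It does not name a participant random effect or a cluster-by-time-point effect, and it does not say whether time is linear or categorical.

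Exposure is coded by current condition: "participants will be categorized based on their current condition (control or intervention) at each time point". Overview and Study Design fixes the switch: "After the third data collection time point, the clusters in the attention control arm will switch to receive the COPE intervention". It also says of the surveys: "Participants will complete assessments at each time point before content delivery". The sections on the two arms confirm this for the three session-based surveys. The Methods paragraph of the Abstract adds that email is used at later time points.

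Sampling Strategies and Sample Size assumes an effect of 0.3, five time points, one ICC of 10% and a within-person correlation of 0.3. It concludes that 15 sites of 20 participants reach 80% power. Potential Limitations expects "external factors, such as in environmental conditions (eg, hurricane season and winter), that may influence the implementation and effectiveness of the intervention" and promises control for cluster, step and season.

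**The concern.** The members of a cluster answer T1, T2 and T3 together, just before a group session. Whatever affected that organization in the preceding week or month (the recall windows of the DASS-21 and PSS in Table 1) can move the whole group at that survey. A cluster intercept is constant over time and a linear slope is a straight line, so neither represents a shift at one survey. A control for step or season is shared by several clusters and does not represent it either.

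The model would then treat the answers of one group at one survey as independent once the cluster's own line is removed. The COPE effect is a contrast of cluster-by-time-point means, so any omitted shared variation in those means makes its standard error too small. The same omission would make the sample-size calculation optimistic, because a single ICC implies a cluster effect that does not change between surveys.

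**Working it through.** **Inputs.** From Sampling Strategies and Sample Size: 15 clusters, m = 20, five surveys, effect 0.3 SD, site variance 0.10, within-person correlation 0.3. Taking total variance as 1, the person variance is 0.3 - 0.1 = 0.2 and the residual is 0.7. From Aim 2 and the switch after T3: the COPE arm is exposed at T2-T5 and the control arm at T4-T5, so the arms differ by d = (0,1,1,0,0). Assumptions not in the documents: an 8/7 split, two-sided 5%, categorical time, a participant intercept, and the cluster autocorrelation (CAC), which is the share of the site variance that persists between surveys. CAC is varied.

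**The plan's own figure first.** Write the covariance of a cluster's five means as aJ + bI (J all ones, I the identity). With categorical time,

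Var = (1/8 + 1/7) / {(1/b)[2 - 4a/(b + 5a)]}.

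At CAC = 1, a = 0.1 + 0.2/20 = 0.11 and b = 0.7/20 = 0.035. The bracket is 2 - 0.44/0.585 = 1.248, so Var = 0.2679/35.65 = 0.00751 and SE = 0.0867. Power = Phi(0.3/0.0867 - 1.96) = 93%. The statement that 300 participants reach 80% is consistent with this. An exact 80% cannot be reproduced, because layout, alpha and formula are not given.

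**Why a slope does not help.** Centred, d is (-0.4, 0.6, 0.6, -0.4, -0.4) and linear time is (-2, -1, 0, 1, 2). Their product is -1.0, so the correlation is -1.0/sqrt(1.2 x 10) = -0.29. A straight line explains about 8% of the pattern.

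**Adding survey-specific shifts.** Now a = 0.1 x CAC + 0.01 and the true b = 0.1 x (1 - CAC) + 0.035. The model without the term sees only b of about [0.7 + 0.1(1 - CAC)]/20. At CAC 0.8 it sees b = 0.036 with a = 0.09 and reports SE = 0.0875. The true SD of that estimator, from the sandwich formula d'F⁻¹VF⁻¹d/(d'F⁻¹d)² times (1/8 + 1/7), with F the fitted and V the true covariance, is 0.1073. The ratio is 0.815: intervals are about 18% too narrow, and the error rate is 2Phi(-1.96 x 0.815) = 11%.

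| CAC | Variance specific to one cluster's survey | Reported SE | True SD | Type I error | If shifts at T1-T3 only |
|---|---|---|---|---|---|
| 1.0 | 0% | 0.0867 | 0.0867 | 5% | 5% |
| 0.95 | 0.5% | 0.0869 | 0.0924 | 6.5% | about 6% |
| 0.9 | 1% | 0.0871 | 0.0977 | 8% | about 7% |
| 0.8 | 2% | 0.0875 | 0.1073 | 11% | about 10% |
| 0.7 | 3% | 0.0878 | 0.1160 | 14% | about 12% |

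This closed form has no slope term. REML simulations that include the linear slope agree: 5.1-5.7% at CAC 1.0, 6.1% at 0.95, 7.6-9.3% at 0.9, 10.6-11.2% at 0.8 and 14.4% at 0.7.

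**With the term added.** Simulated coverage returns to 94.5-95.2% when shifts occur at all five surveys. If they occur at T1-T3 only, a single common variance gives 94.3-94.4% at CAC 0.9 and 93.4-93.9% at 0.8 with a normal reference, which is one reason to use a small-sample reference.

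**Power with the term.** SE is 0.0867, 0.0976, 0.1070 and 0.1152 at CAC 1.0, 0.9, 0.8 and 0.7. With z, power is 93%, 87%, 80% and 74%. With t on 13 df (critical value 2.160, noncentral t with noncentrality 0.3/SE) it is about 89%, 81%, 74% and 67%.

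**The case against.** **The random-effects wording is open.** The figures above assume a participant intercept, which Aim 2 does not name. With only the named kinds of effect, the two omissions partly offset: the error rate is about 2-3% at CAC 1.0, 5-6% at 0.9, 7-8% at 0.8 and 10-11% at 0.7. This stands, and it is a reason to name the participant term as well.

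**Random slopes on categorical time could already be the remedy.** A reader might infer that this reading cannot be fitted. That is true only of the unstructured form, which needs 15 variances and covariances from about 15 clusters. With one common variance it is exactly the term proposed here. The article does not say which is meant.

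**The cited weather does not produce the problem.** Storms and seasons are largely shared by clusters in the same step, and arms are randomized within step. With shifts common to a whole step (assumed sizes 2/4/4/5), the error rate is 5.1-5.3%. This stands: the inflation needs a shift peculiar to one cluster at one survey, and no section describes one.

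**Not every survey is a group sitting.** A reader might infer one sitting per cluster at all five time points. The article supports this for T1-T3 only. The correction changes the size little, because the arms differ in condition at T2-T3.

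**The sizing claim is modest.** The article claims only 80% and reports sensitivity analyses over ICC, correlation and number of sites. With z, 80% holds down to a CAC of 0.8.

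**Conclusion.** The point holds conditionally. The stated cluster-level terms leave out a cluster-by-time-point effect, a linear slope does not stand in for it, and the promised step and season controls do not remove a shift peculiar to one cluster's survey. If such shifts exist, the nominal 5% test runs at roughly 6.5% to 14% for CAC from 0.95 to 0.7, given the article's inputs, an 8/7 split and a participant intercept.

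A reader might conclude that the COPE intervals are too narrow as a matter of fact, and on every outcome. The documents do not support that: they give no autocorrelation, and at 1.0 there is no loss. This is an inexpensive improvement to a model the article does specify, not a demonstrated error in its results.

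**What to change.** In Aim 2, state that time is a categorical fixed effect, name the participant random intercept, and add a cluster-by-time-point random intercept with a single variance. Test the condition effect with a small-sample method (Kenward-Roger, or t on clusters minus 2 df). If the fit fails, use cluster-robust standard errors with a small-sample correction. In Sampling Strategies and Sample Size, state the assumed cluster autocorrelation beside the ICC and give the power for it.

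The cost is a few sentences and one variance parameter. If no such shift exists, the standard error rises about 3% (0.0865 to 0.0891). With t on 13 df, power is then about 87% at SE 0.0891 or 89% at 0.0867, against 93% with z; most of the fall comes from the t reference. It stays above 80%. At a CAC of 0.8, power with the t reference is about 74%, below the target, so the assumed value should be stated openly.
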